### General monitoring

For patients presenting with signs and symptoms relatable to peri-tumoral edema, dexamethasone will be prescribed at a dose level per clinician judgment. For patients presenting with seizure, anti-seizure medication will be prescribed at a dose level per clinician judgment. No specific type of anti-seizure medication is recommended or prohibited. Subjects will be encouraged to remain in the study and maintain regular follow-up. Possible reasons for early withdrawal may include, but are not limited to, the following:Subject decides to withdraw from the study. This decision must be an “independent decision” that is documented in the source documentationThe Principal Investigator and/or treating physician may choose to withdraw a subject from the study if there are safety or other concerns.Subject becomes pregnant.Subject non-compliance.Subject lost to follow-up.Subject death.

### Follow-up

Time-to-event analyses will be measured from the date of completion of radiation therapy (Day 0). As outlined in Table 6 patients will be followed at 1-month post radiosurgery, then at 3 month and every 3 months thereafter for 2 years. A detailed medical history, toxicity assessment and physical examination including vital signs will be performed at each visit. Each follow-up starting from 3 month follow up will also include a MRI with the following sequences: without contrast, with contrast, FLAIR, DTI and PWI. The MRI will be analyzed per RANO-BM criteria [32] for assessment of local control, distant in-brain failure and cranial progression free survival. The MRI will also be analyzed for radiation necrosis and leptomeningeal disease as discussed in methodology section. Cases concerning for radiation necrosis will be further analyzed using MR spectroscopy. After the 2 year follow up period, subjects will be followed according to their treating physician per standard of care approximately every 6 months). Patients will continue to be followed for survival information until death. All AEs considered related to trial medication will be followed until resolution, return to baseline, or deemed clinically insignificant, even if this occurs post-trial.

### Safety considerations

Investigators will conduct continuous review of data and patient safety. Monthly review meetings for moderate risk trials are required and will include the principal investigator, clinical research specialist and/or research nurse. Adverse events (AEs) will be recorded from the time of study intervention and for at least 30 days after treatment discontinuation, regardless of whether or not the event(s) are considered related to trial medications. Any death occurring within 30 days after the study intervention will be reported as a serious adverse event (SAE) regardless of attribution. AEs will be reported to the IRB within 5 days from becoming aware of the event if they are: [1] unexpected, [2] related or possibly related to study participation, and [3] suggests that the research places subject(s) or others at greater risk of harm than was previously known. SAE reports are entered into OnCore® monthly and reviewed by the Data Safety Monitoring Committee (DSMC) chair and/or coordinator monthly. Findings will be reported to the full DSMC at the time of study review. At any time during the trial, the study will be closed early if it is the opinion of the investigators that the risks (or benefits) to the patient warrant early closure of the study. Alternatively, the DSMC may initiate suspension or early closure of the study based on its review of the investigator reports.

### Data management

This study will utilize electronic Case Report Form completion in the OnCore® database. A calendar of events and required forms are available in OnCore®**.** The OnCore® database is a comprehensive, web-based, Clinical Trial Management System (CTMS) which utilizes an Oracle database. All documents will be kept according to applicable federal guidelines. Clinical trial data in OnCore® are periodically monitored by the IU Simon Cancer Center Data Safety Monitoring Committee.

### Quality assurance

Records of IRB review and approval of all documents pertaining to this study will be kept on file in the Clinical Trials Office and are subject to inspection at any time during the study. Periodic status reports will be submitted to the Institutional Review Board at least yearly, as well as notification of completion of the study and a final report within 3 months of study completion or termination. Accrual data will be entered into the IU Simon Cancer Center OnCore® system. The Protocol Progress Committee (PPC) reviews study accrual twice per year while the PPC coordinator reviews accrual quarterly.

### Project Management

Patient recruitment is based on the referral from neurosurgeons, medical oncologists, radiation oncologist, primary care physicians, or self-referral. The principal investigators are responsible for checking eligibility and explaining the study principles, including detailed experimental schedule, investigational treatment, potential risks, and benefits. Radiation oncologists, neurosurgeons, and medical oncologists will be responsible for the consults, clinical treatments and follow up evaluations for the respective specialties. Pathologists will be performing histochemistry, immunochemistry and assist on other aspect of correlative studies. Statistical analysis will be performed by statisticians from the Department of Biostatistics at Indiana University School of Medicine.

### Statistical analysis

A sample size of 44 patients will provide 82% power with an alpha = 0.05 to determine if the proportion of patients with local control at 6 months is <= 83% or > = 95%. For the primary objective of 6-month local control for pre-operative SRS followed by surgical resection of the brain metastases, the proportion of patients who have local control at 6 months will be calculated along with a 95% confidence interval. Testing the observed proportion against a baseline 6-month local control proportion of 83% at a one-sided alpha of 5% using a binomial test will be done. The proportion of patients who have in-brain distant failure, radiation necrosis, and leptomeningeal spread in the evaluated patients will be summarized and exact binomial 95% confidence intervals will be determined. Additionally, time to local failure, distant in-brain progression, and overall survival will be calculated and analyzed using Kaplan-Meier methods with the medians estimated with a 95% confidence interval. The probability rates will be provided for 6 months, 1 year, and 2 years. Finally, the tissue biomarkers of interest in the molecular study will be correlated with treated lesion location, in-brain local control, in-brain distant control, and overall survival using Cox proportional hazards regression. Time dependent ROC curves will be generated to assess predictive ability.

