The first pre-operative SRS study was published by Asher et al where 47 patients were treated consecutively with neoadjuvant SRS before surgical resection, with 24 of those patients analyzed as part of a prospective trial, and the results showed 6-month and 12-month LC rate of 97.8 and 85.6% respectively (Table 3). [28] Subsequently Patel et al performed a multi-institutional retrospective comparison of outcomes and toxicities for pre-operative SRS compared to post-operative SRS for 180 patients. [29] The planning target volume (PTV) of pre-operative SRS had 0 mm margin expansion from gross tumor volume (GTV) compared to 2 mm margin for PTV of post-operative SRS. The study did not note any statistical difference in the rates of local recurrence, distant brain recurrence, and OS but the pre-operative SRS cohort demonstrated significantly lower rates of symptomatic RN (4.9% vs. 16.4%, *p* = 0.01) and LMD (3.2% vs. 16.6%, p = 0.01) than their post-operative SRS counterpart. [29] The abstract of an updated retrospective analysis of 117 patients with 125 lesions treated with pre-op SRS is now available online (https://www.redjournal.org/article/S0360-3016(18)31346-4/fulltext) and reported the 1 and 2-year cavity LC rate to be 80.1 and 74.9%, distant in-brain failure (DBF): 45.3 and 60.2%, and LMD: 4.3 and 4.3%, respectively. Nevertheless, the results were likely limited by some intrinsic selection bias, as the two retrospective cohort groups were statistically different in their baseline performance status (Figure 1).

**Table 3 Tab3:** Published studies of Pre-op SRS prior to Metastases Resection

Study	Treatment Modalities (Number of patients)	Target	Median survival (months)	Outcomes			
				LR (%)	DBF (%)	LMD (%)	Symptomatic RN (%)
Asher, 2014 [28]	PreOP SRS (47)	GTV = PTV	NA	14.4 (1 yr)	38.2 (1 yr)	NA	NA
Patel, 2016 [29]	PreOP SRS (66) Vs. Postop SRS (114)	GTV = PTV PTV = cavity + 1–2 mm margin	17.1 13.5	15.9 (1 yr) 12.6 (1 yr)	32 (1 yr) 39.1(1 yr)	3.2 (1 yr) 3.2 (2 yr) 8.3 (1 yr) 16.6 (2 yr)	4.9 (2 yr) 16.4 (2 yr)
Patel, 2017 [44]	PreOP SRS (66) Vs. Postop WBRT [36]	GTV = PTV PTV = cavity + 1–2 mm margin	13.9 12.6	24.5 (2 yr) 25.1 (2 yr)	53.2 (2 yr) 45 (2 yr)	3.5 (2 yr) 9 (2 yr)	5.6 (2 yr) 0 (2 yr)
Prabhu, 2018 (Abstract only)	Pre-OP SRS (117)	GTV = PTV	17.2	19.9 (1 yr); 25.1 (2 yr)	45.3 (1 yr); 60.2 (2 yr)	4.3 (1 yr); 4.3 (2 yr)	2.6 (1 yr) 4.8 (2 yr)

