### Study population

Patients with 1–4 metastatic lesions in the brain identified on a diagnostic brain MRI or CT with at least one meeting the criteria for surgical resection i.e. symptomatic or size > 3 cm, will be identified as potential study candidates. Amongst the study candidates, patients meeting the inclusion and exclusion criteria (Table 4) will be eligible to enroll in the study. Eligible patients who complete the Informed Consent Process will be registered in the OnCore® database and assigned a patient ID number for the clinical study.

**Table 4 Tab4:** Inclusion and Exclusion Criteria

Inclusion Criteria	
1. Radiographically confirmed solid tumor brain metastases 2. Criteria for surgical resection of at least one metastasis per neurosurgeon discretion 3. A diagnostic MRI Brain or CT Head demonstrating the presence of 1–4 solid tumor brain metastases and lesion to be resected no more than 5 cm in any direction, performed within 30 days prior to stereotactic radiosurgery. If multiple lesions are present, then the total brain metastases volume can be no more than 30 cm^3^ excluding the lesion to be resected. 4. For known primary, ds-GPA estimated median survival no less than 6 months 5. For unknown primary, GPA estimated median survival no less than 6 months 6. Surgical candidate per neurosurgeon discretion 7. Surgical resection able to be performed within 1–4 days after radiosurgery 8. Stereotactic radiosurgery candidate per radiation oncologist 9. ≥ 18 years old at the time of informed consent 10. Ability to provide written informed consent and HIPAA authorization 11. Platelet count > 100 k/ml, Hgb > 7.5 g/dL, INR < 1.3, ANC > 1.5 k/ml 12. Patients currently on cytotoxic chemotherapy or immunotherapy are eligible, not including anti-VEGF therapy	
Exclusion Criteria	

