## Discussion

To date, most studies have evaluated the role of SRS post-operatively in patients with clear indications for surgical management of BMs. [13, 20] We believe that pre-operative SRS merits further investigation as this technique has several clinical and radiobiological advantages, including precise tumor definition, possible sterilization of the tumor margin prior to surgical resection leading to decreased microscopic spread of disease during surgery, removal of irradiated tissue, and a theoretical radiobiological advantage of intact vasculature optimizing oxygenation. Additionally, all prior SRS studies limit indication of SRS to lesion < 4 cm in size due to dose related toxicity. Since we will be resecting the lesion post SRS, we will include lesions up to 5 cm in size.

We expect that, compared with historic LC rate associated with post-operative SRS, pre-operative SRS will have a higher LC rate as well as decreased risk of LMD and symptomatic RN. In terms of radiobiological studies, we expect differential gene expression profile in the tissue from the center of the lesion, which receives 50% greater radiation dose compared to the periphery of the lesion. In addition, we expect to see higher percentage of immune cell infiltrate in the radiation treated lesions.

Our exploratory analysis regarding histologic and molecular changes after radiosurgery will determine if any correlation between immune response to radiation at tumor margin and local control exists. This may characterize a group of patients requiring additional therapy after pre-operative radiosurgery and surgical resection for maximal tumor control.

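### Kaplan-Meier for local and distant brain failure ignores death as a competing event and overstates the share of patients who fail; leptomeningeal spread and necrosis are crude proportions with no time point (secondary endpoints only)

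*Protocol article*

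**What the plan says.** All of the methods are in the Statistical analysis section of the protocol article.

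- **Local failure, distant failure and survival:** "time to local failure, distant in-brain progression, and overall survival will be calculated and analyzed using Kaplan-Meier methods", followed by "The probability rates will be provided for 6 months, 1 year, and 2 years".
- **Distant failure (again), necrosis and leptomeningeal spread:** "The proportion of patients who have in-brain distant failure, radiation necrosis, and leptomeningeal spread in the evaluated patients will be summarized", with exact binomial 95% intervals. The sentence on 6 months, 1 year and 2 years follows the Kaplan-Meier sentence and does not extend to these proportions.
- **Death:** no competing-risk method is named. General monitoring lists "Subject death" among the reasons for early withdrawal.
- **Follow-up:** visits are at 1 month, "then at 3 month and every 3 months thereafter for 2 years".
- **Expected survival:** Table 4 admits patients on the condition "For known primary, ds-GPA estimated median survival no less than 6 months", with a matching GPA rule for an unknown primary.
- **Intended reading of the results:** the Discussion expects, against historic post-operative radiosurgery, that "pre-operative SRS will have a higher LC rate as well as decreased risk of LMD and symptomatic RN".

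**The concern.** Local failure and distant failure are events that death prevents. Kaplan-Meier treats a patient who dies free of failure as someone who could still fail later. With few deaths this hardly matters, but here the cited series have median survival of roughly one to one and a half years and rates are to be given out to 2 years. By then 1-KM no longer estimates the share of treated patients who fail. It estimates a net risk in a hypothetical setting without death, and readers will usually take it for the former.

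The crude proportions raise a different problem. Without a time point, the proportion with leptomeningeal spread or necrosis depends on how long patients happened to be observed, and event-free patients with short follow-up pull it down. Several of the figures a reader would set beside it are tied to a time: leptomeningeal disease of 28% at 12 months in the randomized post-operative trial (Background), and the 1- and 2-year rates in Table 3. Distant failure is also reported both ways, with no statement of which is the result. When many patients die, the two figures will differ.

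**Working it through.** **The plan's own figure.** The exact one-sided binomial test with 44 patients, 83% against 95%, rejects at 41 or more successes. Its actual alpha is 0.0450 and its power 0.8235, so the stated 82% is reproduced. Nothing below changes it.

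**Inputs**
- Local failure 19.9% at 1 year and 25.1% at 2 years; distant failure 45.3% and 60.2% (Table 3, updated pre-operative series, 117 patients). These are read as 1-KM, which is an assumption.
- Median survival 12.2 months (Table 2, multi-center phase III post-operative trial) and 17.2 months (Table 3, updated pre-operative series).
- Assumed: constant death hazard, failure hazard constant within each year, failure independent of death.

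**How common death is.** d = ln 2 / median, which is 0.0568 per month (12.2 months) or 0.0403 (17.2 months). Deaths by t are 1 − exp(−d·t): 49% or 38% by 1 year, and 74% or 62% by 2 years.

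**Formulas.** With 1-KM of K1 at 12 months and K2 at 24 months:
- λ1 = −ln(1 − K1)/12 and λ2 = −ln[(1 − K2)/(1 − K1)]/12
- CIF(12) = λ1/(λ1 + d) × [1 − exp(−12(λ1 + d))]
- CIF(24) = CIF(12) + exp(−12(λ1 + d)) × λ2/(λ2 + d) × [1 − exp(−12(λ2 + d))]

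**Worked case: local failure, median 12.2 months.** λ1 = −ln(0.801)/12 = 0.01849 and λ2 = −ln(0.749/0.801)/12 = 0.00559.
- CIF(12) = 0.2455 × (1 − 0.4051) = 0.146
- CIF(24) = 0.146 + 0.4051 × 0.0896 × 0.5271 = 0.146 + 0.019 = 0.165

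**Results**

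| Endpoint | Time | 1-KM | Cumulative incidence (median 12.2 to 17.2 months) | Excess of 1-KM, points |
|---|---|---|---|---|
| Local failure | 1 year | 19.9% | 14.6% to 15.9% | 5.3 to 4.0 |
| Local failure | 2 years | 25.1% | 16.5% to 18.5% | 8.6 to 6.6 |
| Distant failure | 1 year | 45.3% | 34.0% to 36.8% | 11.3 to 8.5 |
| Distant failure | 2 years | 60.2% | 39.5% to 44.2% | 20.7 to 16.0 |

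At 6 months the gap is small. A 1-KM of 5% (the design alternative of 95% control) corresponds to 4.2% to 4.4%, and a 1-KM of 17% (the 83% null) to 14.5% to 15.2%.

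**Crude proportions.** Take a leptomeningeal hazard matching 8.3% net at 1 year (Table 3, post-operative cohort of the multi-institutional comparison): λ = −ln(0.917)/12 = 0.00722 per month. With death competing, the proportion observed if everyone is followed for the same time is 3.6% to 3.8% at 6 months, 6.0% to 6.6% at 12 months and 8.9% to 10.3% at 24 months. The same disease process can therefore give about 4% or about 10%, depending only on length of follow-up.

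**The case against.** - **Kaplan-Meier is not invalid.** If censoring by death is independent, it estimates a net risk, and the article never writes out a censoring rule. This stands. The overstatement concerns 1-KM read as the actual probability of failure. Censoring at death is inferred from applying the method to endpoints that do not include death.
- **Comparison with the benchmarks.** A reader might infer that the local and distant rates cannot be compared with the cited series. The documents do not support that, because they do not say which estimator those series used. If it was Kaplan-Meier, the comparison is like with like. If it was cumulative incidence, the trial's Kaplan-Meier rates would look worse, against the hoped-for benefit: a cumulative incidence of 19.9% at 1 year corresponds to a 1-KM of about 25% to 27%.
- **Larger 2-year gaps.** Extending the 1-year hazard unchanged gives 1 − 0.547² = 70% distant and 1 − 0.801² = 36% local failure at 2 years, and so wider gaps. Those figures contradict the 60.2% and 25.1% in the same Table 3 row and should not be used.
- **Crude proportions.** With complete follow-up to a fixed time, the crude proportion equals the Aalen-Johansen estimate. An event-free patient who dies at month 2 stays in the denominator of both, so early death is no argument against the crude figure. The downward bias comes only from administrative censoring or loss to follow-up, and the documents do not allow its extent to be estimated.
- **A manufactured benefit.** A reader might infer that the plan would create the lower leptomeningeal and necrosis risk that the Discussion expects. That goes too far. The expectation is a discussion statement, no test of either endpoint against a benchmark is planned, and several cited figures (most of Table 2, the 13% leptomeningeal rate) are not rates at a fixed time either.
- **The unseen analysis plan.** It may add a time point for the proportions. The Kaplan-Meier choice, however, is a method this document fixes, not a detail it leaves open.

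**Conclusion.** The point holds for the secondary endpoints. Under the stated assumptions, 1-KM exceeds the cumulative incidence of local failure by about 4 to 5 points at 1 year and 7 to 9 at 2 years, and that of distant failure by about 8 to 11 and 16 to 21 points. At 6 months the difference is minor. The sizes rest on reading the Table 3 rates as 1-KM, on independence of failure and death, and on the two medians chosen. Table 2 medians run from 8.9 to 20 months; a shorter median widens the gap and a longer one narrows it.

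For leptomeningeal spread and necrosis the defect is the missing time point. The proportions depend on follow-up and understate risk where it is incomplete, but by how much cannot be derived here. The primary 6-month test and its power stand as written.

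**What to change.** Estimate local failure, distant in-brain failure, leptomeningeal spread and radiation necrosis by Aalen-Johansen cumulative incidence, with death as a competing event, and report each at 6, 12 and 24 months with 95% confidence intervals. Keep Kaplan-Meier for overall survival and for intracranial progression-free survival, where death is itself an event. Keep the Kaplan-Meier local-control and distant-control rates as labelled sensitivity results, since the estimator behind the cited series is not given.

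The cost is wording and standard software. Event dates and dates of death come from follow-up already scheduled, so no visits or patients are added. The one drawback is that local and distant control will each appear in two versions, which must be clearly labelled.

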## Discussion

To date, most studies have evaluated the role of SRS post-operatively in patients with clear indications for surgical management of BMs. [13, 20] We believe that pre-operative SRS merits further investigation as this technique has several clinical and radiobiological advantages, including precise tumor definition, possible sterilization of the tumor margin prior to surgical resection leading to decreased microscopic spread of disease during surgery, removal of irradiated tissue, and a theoretical radiobiological advantage of intact vasculature optimizing oxygenation. Additionally, all prior SRS studies limit indication of SRS to lesion < 4 cm in size due to dose related toxicity. Since we will be resecting the lesion post SRS, we will include lesions up to 5 cm in size.

We expect that, compared with historic LC rate associated with post-operative SRS, pre-operative SRS will have a higher LC rate as well as decreased risk of LMD and symptomatic RN. In terms of radiobiological studies, we expect differential gene expression profile in the tissue from the center of the lesion, which receives 50% greater radiation dose compared to the periphery of the lesion. In addition, we expect to see higher percentage of immune cell infiltrate in the radiation treated lesions.

Our exploratory analysis regarding histologic and molecular changes after radiosurgery will determine if any correlation between immune response to radiation at tumor margin and local control exists. This may characterize a group of patients requiring additional therapy after pre-operative radiosurgery and surgical resection for maximal tumor control.

## Abbreviations

BM: Brain metastasis
DBF: Distant-in-brain failure
ECOG: Eastern Cooperative Oncology Group
GPA/ds-GPA: Graded prognostic assessment/Diagnosis-specific graded prognostic assessment
GTV: Gross target volume
KPS: Karnofsky Performance Status
LC: Local control
LMD: Leptomeningeal disease
LR: Local recurrence
OS: Overall survival
PTV: Planning target volume
RN: Radiation necrosis
SRS: Stereotactic radiosurgery
WBRT: Whole brain radiation therapy
